### Evidence-based intervention

RT4T is an 8-week multicomponent physical activity programme, including practical and theory-based lessons designed to develop adolescents’ knowledge, competence, confidence and motivation to participate in muscle strengthening activity. The design and delivery of RT4T is guided by the Supportive, Active, Autonomous, Fair and Enjoyable (SAAFE) principles for organised physical activity sessions for school-aged youth.^38^ The training sessions and progressions were revised based on the Youth Physical Development Centre Basic Resistance Training Curriculum developed by Radnor *et al*.^39^

The RT4T programme includes four major components: (1) school-based RT sessions (delivered by teachers); (2) theoretical classroom sessions (delivered by teachers); (3) a smartphone and tablet app (used by students/teachers) and (4) energiser breaks (used by teacher during theoretical sessions).

### School-based RT sessions

Teachers will deliver the RT4T programme during their usual PE lessons, co-curricular school sport or Physical Activity and Sports Studies lessons. The RT4T practical sessions include four subcomponents: (1) movement based dynamic warm-up (5 min), (2) RT skill development (GymFit: 15–20 min) focused on five RT movement categories (ie, upper body push, upper body pull, lower body bilateral, lower body spilt and core stability), (3) choice of three different types of muscle strengthening activities: a fitness workout of the day (WOD), modified game with fitness infusion (GameFit), or a fun fitness challenge done to music (FunFit) (15–20 min); and (4) cool down and static stretching (StretchFit: 5 min). Practical sessions will be supported using a variety of resources, including exercise cards (see figure 1) and the RT4T smartphone and tablet app (see figure 2). Teachers will be also provided with a handbook that includes all the practical activities and theoretical content.

**Figure 1 F1:**
[figure not shown]
Resistance Training for Teens exercise cards (front and back side).

**Figure 2 F2:**
[figure not shown]
Resistance Training for Teens app.

### Theoretical classroom-based lessons

Students will receive 8×40 min theory-based lessons that accompany weekly practical lessons. Content is purposefully aligned with the Australian curriculum for Health and Physical Education^40^ and Australian Physical Literacy Framework.^41^ The lesson topics are generally relevant to RT and adolescent health. Topics include: (1) introduction to RT, (2) fitness, self-assessment and self-monitoring, (3) fitness and e-Health technologies, (4) principles of training and RT programme design, (5) nutrition and RT: myths and recommendations, (6) social media, physical activity and body image, (7) yoga, Pilates and other community-based muscle strengthening activity and (8) reviewing fitness outcomes and realigning future goals.

### Smartphone and tablet app

We have developed and updated IOS and Android versions of the RT4T smartphone and tablet app to support teachers to implement the programme (see figure 2). Use of the app is optional and includes: (1) fitness testing, (2) evaluating RT skill competence, (3) pre-designed or customisable RT workouts and (4) an exercise library enabling users to browse bodyweight exercises organised by the five RT movement categories.

### Implementation strategies that support teachers to deliver RT4T

We will assess whether implementation strategies can be implemented effectively across three study arms that offer implementation support. We define implementation strategies as methods or techniques used to enhance adoption, implementation or sustainability of the evidence-based intervention.^42^ Study arms are (1) low support or ‘usual practice’ (training and resources), (2) moderate support (training and resources+external support) and (3) high support (training and resources+external support+equipment) (see table 1). Implementation strategies were codeveloped with our partners in the NSW Department of Education and NSW local health districts and guided by findings from our previous dissemination study.^28^ Our strategies align with the taxonomy of strategies as described by Proctor *et al*.^42^

**Table 1 T1:** Domains, constructs and strategies used in our three implementation support models

Domains	Constructs	Strategies	Level of support		
			Low	Moderate	High
RT4T intervention	Evidence strength/quality	Findings from the RT4T cluster randomised controlled trial were used in promotional and training materials.	✔	✔	✔
	Adaptability	Flexible intervention delivery model (physical education, school sport or elective) requiring minimal access to equipment.	✔	✔	✔
	Design quality and packaging	Programme resources developed by a professional graphic designer.	✔	✔	✔
Outer setting	Partnerships and investment	Investment from, and partnership with, key stakeholders from education (ie, NSW Department of Education) and health (ie, NSW Health local health districts).	✔	✔	✔
	External policy and incentives	Professional learning accreditation with national-based and state-based educational standards authorities. Alignment with state school physical activity policy.	✔	✔	✔
Inner setting	School culture	School champions will run a 2-hour face-to-face professional development workshop for other teachers in their school on RT4T. Prior to this, the teachers will have completed a 30 min prelearning session on resistance training safety. In the 2-hour workshop, the school champion will: Present the evidence and the rationale of RT4T. Teachers will participate in RT4T activities, discuss the content and gain consensus on how they will deliver RT4T. The school champion will share and explain the resources they received at the school champion workshop.	✔	✔	✔
	Leadership engagement	School champions and project officers will have approximately five contacts (three online and two face to face). In these meetings, they will: Discuss the action plan which was created by the school champion during the full-day workshop. Discuss the outline of the 2-hour training content. Evaluate two RT4T practical sessions, observed by the project officer and delivered by the school champion or another teacher who completed the 2-hour training delivered by the school champion.		✔	✔
	Resources	Schools will receive exercise technique and workout resources. These will be provided to the school champion at the teacher workshop. All materials will also be available on a website where teacher can upload all the materials they need to deliver the programme.	✔	✔	✔
	Equipment	Schools will be provided with a basic RT equipment pack (~$A1000). This includes 4×5 kg weighted bars, 4×3 kg dumbbells, 2× portable pull up bar stands and 4× sets of resistance bands. These will be delivered to the schools in the high support group following randomisation after the workshop.			✔
Individuals	Capability, opportunity, motivation (teacher)	A full-day professional development workshop will be provided to school champions. This workshop will be accredited with the NSW Educational Standards Authority and counts towards teachers professional learning. This will be delivered by the research team (UoN) who are experts in resistance training and school interventions. These will be held for groups of schools in the local area convenient to their location. Teacher relief for the school champions will be provided by the School Sport Unit (government schools) and University of Newcastle (non-government schools) to the school to cover the cost of their attendance. Prior to attending the workshop, school champions will complete the 30 min online prelearning on resistance training safety. The full-day workshop training will cover the following: Rationale for RT4T (ie, prevalence of physical inactivity in youth, benefits of RT and myths/facts regarding participation in RT). Adaptability of RT4T. Skills and demonstrations of the movements. RT4T lesson content and alignment with the Personal Development, Health, and Physical Education syllabus. Roles and responsibilities of school champions, teachers, and project officers. Introduction to the RT4T app.	✔	✔	✔
	Perceived barriers (student)	Addresses student motivation using SAAFE principles. Teachers will learn to deliver RT4T using the SAAFE principles.	✔	✔	✔
Implementation process	Planning for implementation	Teachers will complete an action plan template to support implementation of RT4T in their school. The action plan will include: When they are going to train their staff and how. When they are going to get resources to teachers and how. Roles and responsibilities of the school champion and teachers. School champions will complete the action plan during the full-day professional development workshop.	✔	✔	✔
	Project officers	School champions will be connected to a project officer who will provide ongoing support to the school champions after they have attended the workshop. The project officer will: Attend in person meetings with the school champion to gain commitment. Email/phone/visit the school champions. Support teachers via a closed RT4T Facebook group, which is created by the project manager from RT4T. Complete the checklist as part of the project officer handbook, which is developed by the research team. Stay in touch with the project manager from RT4T and provide all the needed details that are requested by the research team (eg, keep track of the support provided and join the weekly 10-min drop in meetings).		✔	✔
	Evaluation and feedback	The project officers will observe approximately two RT4T session per school and provide feedback on the RT4T structure via email. Observations will be conducted using a standardised checklist developed by the research team that assesses aspects of the RT4T session (eg, did the teachers conduct the warm-up?). Project officers will only provide feedback on the RT4T structure via email.		✔	✔

NSW, New South Wales; RT4T, Resistance Training for Teens; SAAFE, Supportive, Active, Autonomous, Fair and Enjoyable; UoN, University of Newcastle.

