### Participants

#### Teachers

One or two teachers from each enrolled school who teach students in grades 9 and 10 will be recruited to act as a ‘school champion’. They will attend a single full-day professional learning workshop delivered by members of the research team with tertiary qualifications in physical education (PE), health promotion, exercise physiology and/or strength and conditioning. School champions will receive curriculum materials and resources at the workshop and will be asked to deliver a separate 2-hour training for other grade 9 and 10 teachers at their schools, who also have the option to implement the programme with their classes. Teachers can deliver the RT4T sessions to their students during usual PE lessons, co-curricular school sport periods or within an elective subject known as Physical Activity and Sports Studies. Professional learning will align with the NSW Educational Standards Authority accreditation process. Lastly, the learning will contribute to teachers’ required annual training hours.^35 36^

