### Sample size calculation

We aim to recruit 90 secondary schools, with 30 schools assigned to each of the three treatment arms. This will include an estimated 261 classes and n=~7800 students across the three arms of the trial. Based on our previous research in secondary schools, we estimate 20% of schools will not provide usable data for our primary outcome at follow-up. As few studies have tested the effects of implementation strategies on the reach of the school-based physical activity interventions, there is little information to guide power calculations. Therefore, we estimated that the low support group will achieve 12.5% reach, while both the moderate and high support groups will achieve 25% reach (ie, between-group difference of 12.5%). Our power calculation is based on 90% power, type 1 error rate of 0.025 and SD of 12%. For the continuous secondary student effectiveness outcomes, we assumed an intraclass correlation coefficient estimate of 0.2. If 10% of schools provide usable data (~780 students), our study will have 80% power to detect significant small-to-moderate effects between the treatment arms.

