### Blinding and randomisation

After teachers have completed the RT4T workshop, schools will be randomised to one of three implementation support arms. Schools will be stratified by school type, socioeconomic status and location and randomised using a random number producing algorithm by an independent statistical analysis service. Data analysis will be conducted by individuals blinded to group allocation.

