### Statistical analysis

Statistical analyses will be conducted by an independent statistical analysis service—Clinical Research Design, Information Technology and Statistical Support from Hunter Medical Research Institute. Analyses of the primary (programme reach) and secondary outcomes will be conducted using logistic mixed models (SAS Institute, Cary, North Carolina, USA) for dichotomous outcomes, and ordinal or linear mixed effects regression models for continuous outcomes. The primary outcome (ie, reach) will be collected at the school level and assessed using t-tests. Alpha levels will be set at p<0.025 for the comparisons of the moderate and high support arms against the low support arm. If the p values for the differences between the moderate and high support arms with the low support arm reach this threshold, the moderate and high support arms will be compared at a 5% significance threshold. For student-level outcomes, statistical analyses will be adjusted for the clustering of effects at the class level, as students from each school are nested in classes. Although clustering at the school level is negligible after adjusting for clustering at the class level, we will test this assumption and adjust our analyses for school-level clustering if required. For teacher-level outcomes, clustering will be accounted for at the school level. Two potential moderators of effects will be explored using interaction terms (ie, socioeconomic status of school and school location). School socioeconomic status will be determined using the Index of Community Socio-Educational Advantage (ICSEA), which will be obtained from the MySchool website.^60^ School ICSEA values are determined using student-level parent occupation and education data, school location (ie, remoteness), and percentage of indigenous student enrolment.

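### The t-test named for school-level reach uses no pre-randomisation information; recording intended delivery before allocation and adjusting for it with the strata would be an optional gain in precision

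*Protocol article*

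**What the plan says.** **Analysis of reach.** Statistical analysis states: "The primary outcome (ie, reach) will be collected at the school level and assessed using t-tests". No covariate is given. The sentence before it lists reach among the outcomes to be analysed with mixed models, so the section is not consistent about the method; that sentence names no covariate either. School socioeconomic status and location appear later in the section, but only as moderators to be explored through interaction terms.

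**Timing.** Under Blinding and randomisation: "After teachers have completed the RT4T workshop, schools will be randomised to one of three implementation support arms". Schools are stratified by type, socioeconomic status and location. Reach is taken from teacher logbooks at T1 and T2, so there is no T0 value.

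**What is recorded before allocation.** Table 1 (Planning for implementation, ticked for all three arms) says: "School champions will complete the action plan during the full-day professional development workshop". The listed contents are staff training, distribution of resources, and roles. A teacher survey is also planned at T0. Its constructs, listed under Implementation determinants, include capability, opportunity and motivation, but not planned volume or setting of delivery.

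**Choice of setting.** Under Teachers: "Teachers can deliver the RT4T sessions to their students during usual PE lessons, co-curricular school sport periods or within an elective subject".

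**The concern.** A school's reach is largely a matter of how many classes take part and where. The plan expects 261 classes in 90 schools, about 2.9 per school (261/90), so a few whole classes make up each school's numerator. A school that delivers only in an elective can reach only the students who take it, whereas usual PE is open to more of the year group. Champions may already have a view on this at the workshop, before anyone knows the arm. If so, part of the between-school variance in reach is predictable at baseline. A t-test leaves that part in the error term, together with whatever the stratification factors explain.

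Timing also matters. A later analysis plan can add covariates, but only from data already collected. After allocation, project officers discuss the action plan with champions in the moderate and high arms only, so intentions recorded then could depend on arm.

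At stake is the precision of the two primary comparisons and of moderate versus high. The latter has no assumed difference behind it, since the plan expects 25% reach in both arms.

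**Working it through.** **Inputs from Sample size calculation**
- Design inputs: "Our power calculation is based on 90% power, type 1 error rate of 0.025 and SD of 12" percentage points. Sidedness is not stated.
- Effect: "we estimated that the low support group will achieve 12.5% reach, while both the moderate and high support groups will achieve 25% reach", a difference of 12.5 points.
- Schools: "We aim to recruit 90 secondary schools, with 30 schools assigned to each of the three treatment arms".
- Loss: "we estimate 20% of schools will not provide usable data for our primary outcome at follow-up", so 30 × 0.8 = 24 usable schools per arm.

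**Step 1: reproduce the plan's figure.** By the normal formula with two-sided alpha 0.025, n = 2 × (12/12.5)² × (2.241 + 1.282)² = 1.8432 × 12.41 ≈ 22.9, so 23 per arm. Allowing for loss, 23/0.8 = 28.75, so 29, close to the stated 30. One-sided 0.025 would give 20, inflated to 25, so two-sided is the matching reading.

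**Step 2: power of the planned t-test.** With 24 schools per arm:
- standard error = 12 × √(2/24) = 3.464
- noncentrality = 12.5/3.464 = 3.608, on 46 degrees of freedom
- power = 89.8% by the noncentral t (91.4% by the normal approximation)

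The t-test therefore meets its target within rounding.

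**Step 3: add one baseline covariate.** Let r be the correlation of intended with achieved reach within arm. The document gives no value, so r is an assumption. The residual SD is 12 × √(1 − r²), and one degree of freedom is lost. For r = 0.5 the SD is 10.39, the standard error 3.00 and the noncentrality 4.167.

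| Assumed r | Residual SD | Power for 12.5 points (alpha 0.025) | Detectable moderate vs high (80% power, 5%) | Unadjusted schools per arm for equal precision, 24/(1 − r²) |
|---|---|---|---|---|
| t-test, no covariate | 12.00 | 89.8% | 9.9 points | 24.0 |
| 0 | 12.00 | 89.7% | – | 24.0 |
| 0.2 | 11.76 | 90.9% | 9.7 | 25.0 |
| 0.3 | 11.45 | 92.4% | 9.5 | 26.4 |
| 0.5 | 10.39 | 96.5% | 8.6 | 32.0 |

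**Step 4: cost of the extra terms.** Suppose intended reach and the stratification terms together used six degrees of freedom (an assumption, since the number of stratum levels is not given), leaving 40. If none of them predicted reach, power would be 89.5%, a loss of 0.3 points. With r = 0.3 for intended reach and nothing from the strata, it would be 92.2%.

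**The case against.** The case against is substantial, and much of it stands.

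**The text contains no error on this point.** The action plan sentence is correct, and covariate lists and form contents are commonly left to a fuller document. That is why this is an optional improvement. What keeps it alive is that the article does fix a t-test for the primary outcome, and that an item not collected before allocation cannot be recovered later.

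**Other predictors exist.** A reader might infer that intended delivery is the only natural baseline predictor the trial has. The document does not support that: the three stratification factors and the T0 survey are also there. Intended delivery is only the most direct proxy. The t-test leaves the strata out as well, so they belong in the same model.

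**The action plan may already ask.** Table 1 gives a summary list that need not be complete, and the template is not shown. If the item exists, only the model needs changing.

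**The champion may not know.** By Table 1, a school settles how it will deliver at the later two-hour in-school session, and other teachers may opt in. The figure would be one person's intention. Project officer support could also make the link between intention and delivery differ by arm. Both points argue for a low r. Neither biases a comparison adjusted for a value recorded before allocation.

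**The action plan is part of the intervention.** Asking champions there to commit to numbers could act as goal-setting, including in the low arm that represents usual practice. This stands, and it favours the T0 survey.

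**Imputation.** It is tempting to use intended reach to fill in the 20% of schools expected to have no usable data. Some of them may have no logbooks because they never delivered, and their intentions would then overstate reach.

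**Conclusion.** The point holds as a modest, optional gain in precision. The t-test on reach uses neither the stratification factors nor any measure of intended delivery, and intended delivery is not among the items listed for collection before allocation.

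The gain is 1 to 3 percentage points of power at r = 0.2 to 0.3 and about 7 points at r = 0.5. The detectable moderate-versus-high difference shrinks by 0.2 to 0.4 points, or by 1.3 points at r = 0.5. All of this rests on a correlation the document does not give, on the stated SD of 12, and on 24 usable schools per arm.

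A reader might infer that the trial is underpowered or its primary comparison biased. Neither follows. The stated sample size reproduces, the t-test has about 90% power under the plan's inputs, and randomisation with its error rate already covers chance imbalance in planned delivery.

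**What to change.** 1. Before allocation, ask each champion for the planned number of grade 9 and 10 classes and students to receive RT4T in the two-term window, and the planned setting (PE, school sport or elective). Put these items preferably in the T0 teacher survey, leaving the action plan unchanged, and state that the champion's answers must be in before the school is randomised.
2. Define intended reach as planned students divided by grade 9 and 10 enrolment.
3. Replace the t-test with one prespecified school-level linear model of reach on arm, stratification factors and intended reach, and remove the conflict with the mixed-model sentence. Keep the alpha levels and the order of comparisons as they are.
4. Do not rely on intended reach alone to impute schools without logbooks. Pair any such imputation with a sensitivity analysis that sets their reach to zero.

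The cost is a few survey items, one changed model statement and a few degrees of freedom. The sample size need not change. If champions' intentions prove uninformative, the loss is about 0.1 points of power for that covariate.

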### Implementation framework and strategies

Our approach is guided by the Consolidated Framework for Implementation Research (CFIR), which describes constructs across five domains: (1) intervention characteristics (RT4T), (2) outer settings (NSW Department of Education), (3) inner setting (schools), (4) individual (student/teacher) characteristics and (5) the process of implementation.^43^ We describe relevant implementation strategies in table 1. We categorised implementation strategies as per the CFIR constructs and specified their usage using the Action, Actor, Context, Target, Time framework.^44^

